#### 2.3.7. Shedding Criteria

Natural shedding and loss of follow-up during observation may occur during the trial. He/she will quit by himself/herself if it is not suitable to continue participating in the trial because of severe complications or unpredictable events. Shedding cases should be documented in detail, and intention-to-treat (ITT) analysis should be performed in the end.

#### 2.3.8. Trial Suspension Criteria

It is essential to suspend the trial if serious safety problems occur during the process of trial. The chief supervisor will be in charge of dealing with this particular situation when it occurs. Critical issues should be recorded in detail and handled properly. All collected data will only be analyzed in the end, and no planned interim analyses will be performed.

### 2.4. Randomization and Blinding

A simple random method is adopted, and SPSS (version 21.0) software will be used by independent biostatisticians to generate random number sequences. Written informed consent should be signed immediately by himself/herself, agreeing to voluntarily enroll in the trial. Participants should be consented for randomization and participation. According to the sequence of enrolling in clinical observation, participants will be randomly numbered and divided into the RG group, the CHF group, and the RG + CHF group by investigators at 1 : 1 : 1 ratio. During randomization producer, sealed envelopes marked with sequential coding numbers will be adopted to keep allocation details, and group allocation should be kept blind to patients, biostatisticians, and investigators. As placebo is not used in the control group, it is not possible to be blind in the treatment. However, it is masked from staff performing all laboratory investigations.

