### 2.2. Study Design and Setting

This is a multicenter randomized controlled clinical trial in which participants will be recruited from the department of nephrology. Three hospitals are listed below: (1) Shanghai Municipal Hospital of Traditional Chinese Medicine; (2) Shuguang Hospital Affiliated to Shanghai University of Traditional Chinese Medicine; and (3) Minhang Branch of Yueyang Hospital of Integrative Chinese and Western Medicine Affiliated to Shanghai University of Traditional Chinese Medicine.

The design of this trial follows strict scientific clinical research methodology and complies with principles of *the Declaration of Helsinki* [34] and *the Guidelines for Good Clinical Practice* [35].

This trial is registered in the Chinese Clinical Trial Register (No. ChiCTR2100043311). The study flow chart is shown in Figure 1.

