#### 2.3.4. Inclusion Criteria

Participants will be enrolled in the trial if they satisfy all the following criteria: (1) meet the diagnostic criteria for CKD stages 2–4 and AKI grades 1–2; (2) meet the diagnostic criteria of TCM syndrome differentiation; (3) 24 h U-pro ≤2.5 g; (4) between 18 and 70 years old; and (5) voluntary to be enrolled in the clinical trial and sign informed consents.

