### 2.9. Sample Size Estimation

The sample size will be calculated according to the primary outcome of baseline Scr change. Based on previous studies and literature reports [26, 30], the mean value of Scr was 160.39 *μ*mol/l, and the standard deviation was 44.43 *μ*mol/l. We thus hypothesize that Scr for CHF combing RG group would be significantly lower than the other two groups by more than 30 *μ*mol/l. It is calculated using the sample size estimation software PASS (version 15.0.3) to achieve test efficacy 1–*β* = 0.90 and significant difference *α* = 0.05 (one-sided test). Considering 20% drop rate, the estimated sample size for randomization will be 54 cases in each group for a total of 162 cases.

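### Simple randomisation without blocks or strata, and a primary analysis with no hospital or AKI-grade term, leave balance on both factors to chance in a small three-arm, three-hospital trial.

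*Protocol article*

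**What the plan says.** All references are to the protocol article.

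- **Method (2.4).** "A simple random method is adopted, and SPSS (version 21.0) software will be used by independent biostatisticians to generate random number sequences". Patients are numbered in order of enrolment and divided into "the RG group, the CHF group, and the RG + CHF group by investigators at 1 : 1 : 1 ratio". Neither a block nor a stratum is mentioned.
- **Concealment and blinding (2.4).** "sealed envelopes marked with sequential coding numbers will be adopted to keep allocation details". On blinding: "As placebo is not used in the control group, it is not possible to be blind in the treatment". Laboratory staff are masked.
- **Setting (2.2).** "Three hospitals are listed below", followed by three Shanghai hospitals. Expected recruitment per hospital is not given.
- **Severity range (2.3.4).** Patients must "meet the diagnostic criteria for CKD stages 2–4 and AKI grades 1–2". Table 1 defines the grades by the rise in serum creatinine (Scr) over baseline or by urine output. The expected mix of grades is not given.
- **Size (2.9).** The target is "54 cases in each group for a total of 162 cases", after allowing for 20% dropout.
- **Analysis (2.10).** Scr is to be compared by a one-way repeated-measures ANOVA. No term for hospital or AKI grade is named.

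**The concern.** An unrestricted random sequence gives equal arms only on average. It also does nothing to keep the arms alike within each hospital or within each AKI grade.

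Both factors could matter here. Grade can be set by the rise in Scr, and the primary outcome is built from Scr, so grade is a plausible prognostic factor. General treatment in section 2.5 is described by its aims, which leaves room for practice to differ between hospitals. With about 54 patients per arm, a chance imbalance on either factor adds noise to the treatment contrasts and makes a positive or negative result harder to read. The analysis named in section 2.10 would not take that noise out.

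**Working it through.** **Inputs from the article:** 162 patients, three arms at 1:1:1, three hospitals, 20% dropout, SD 44.43 μmol/l, difference 30 μmol/l, α = 0.05, power 0.90.

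**Assumed, because the article gives no figure:** hospital sizes (54 each, or 81/49/32, or 100/40/22), grade-2 share (20% to 50%) and block sizes.

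**1. The planned size.** The 54 per arm is reproduced by a three-arm ANOVA F-test with means 0, 0, −30. The grand mean is −10 and the squared deviations sum to 100 + 100 + 400 = 600. With 43 per arm the noncentrality is 43 × 600 / 44.43² = 13.07 and power is 90.3%; with 42 it is 89.5%. Then 43 / 0.80 = 53.75, rounded up to 54.

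**2. Arm sizes under an unrestricted sequence.**
- SD of one arm = √(162 × 1/3 × 2/3) = √36 = 6.0.
- P(54/54/54) = 162! / (54!³ × 3¹⁶²) = 0.0051, or 0.5%.
- By simulation, the gap between largest and smallest arm averages 12.4 (median 12). It is 20 or more in 15% of runs.

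**3. What that costs in power.** With 80% retained, the F-test has 90.4% power at 54/54/54. Over simulated arm sizes it averages 90.1%, with a 5th percentile of 86.6%. The average loss is 0.3 points.

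**4. Balance on hospital.** Take one hospital that supplies a third of the patients. The difference in its share between two given arms has SD ≈ √(2 × 1/3 × 2/3 / 54) = 0.091 (simulated 0.092). P(difference ≥ 10 points) is about 28% by simulation. For the largest hospital under the two unequal splits it is 29% to 30%.

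**5. Balance on AKI grade.** The same formula with grade-2 share p gives SD ≈ √(2p(1 − p)/54).

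| Grade-2 share | SD by formula | P(≥ 10 points), simulated | P(≥ 15 points), simulated |
|---|---|---|---|
| 20% | 0.077 | 20% | 5% |
| 50% | 0.096 | 30% | 12% |

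**6. What an imbalance would do.** If grade-2 and grade-1 patients differ by D in the outcome, a 10-point imbalance shifts an unadjusted contrast by 0.10 × D. The article does not give D. If D were as large as the planned 30 μmol/l, the shift would be 3 μmol/l, a tenth of the planned effect.

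**7. What restriction achieves.**
- *Blocks of 6 by hospital only.* With unequal hospitals the mean gap in arm size falls to about 2. Grade balance hardly changes: the SD of the difference in grade-2 share is 0.088 to 0.096, against 0.089 to 0.097 under simple randomisation (share 30% to 50%).
- *Blocks of 3, 6 or 9 by hospital and grade (six strata).* The mean gap is about 2.4 to 2.9. No difference of 10 points or more in grade-2 share, or in the first-listed hospital's share, occurred between two given arms in 5,000 runs per scenario. Scenarios were the three site splits with grade-2 shares of 20%, 40% and 50%.

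**8. The price in predictability.** If earlier allocations at a site are known, the last of every block of 3 is certain: 1/3 = 33%. In a fixed block of 6 the last is certain, and the fifth is too with probability 1/5: 1.2/6 = 20%.

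**The case against.** Simple randomisation is a legitimate method. It balances every factor in expectation and supports valid tests. In an open-label trial where investigators allocate from envelopes, it is also the least predictable choice. Centralised training and a central laboratory (section 2.11) may limit differences between hospitals, and the article gives no figure for the effect of hospital or grade on Scr. An analysis plan that is not shown may name covariates. All of this stands, and it keeps the point at the level of an improvement.

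Four stronger readings are tempting, and the document supports none of them.

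- *The trial will almost never have 54 per arm, so its power is undermined.* The 0.5% applies only if the sequence is unrestricted. The wording in section 2.4 could also mean a random ordering of a fixed 54/54/54 list, which gives exact totals once 162 are enrolled. Even when the sequence is unrestricted, nothing in the analysis needs equal arms and the average loss is 0.3 points. Stratified blocks usually miss exact equality too, by two or three patients.
- *The arms will be unbalanced, or the comparison biased.* The risk is chance imbalance; the method introduces no systematic bias.
- *Blocking by hospital would also balance grade.* Step 7 shows that it would not.
- *The change is free.* Step 8 shows a real, if limited, loss of unpredictability.

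The fixed-list reading does not remove the point: balance on hospital and grade would still be left to chance.

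**Conclusion.** The point holds as a modest design weakness. The article commits to simple randomisation with no block or stratum and names a primary analysis without hospital or AKI grade. Arm sizes (if the sequence is unrestricted) and balance on both factors are therefore left to chance. The case for change rests on balance, since the power argument is negligible. The 28% for a hospital's share assumes equal hospitals, and the 20% to 30% for grade assumes a grade-2 share of 20% to 50%. How far such an imbalance would move the result depends on prognostic effects that the article does not report, so the harm can be described as a risk but not given a firm size.

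**What to change.** 1. In section 2.4, state 1:1:1 allocation in permuted blocks of randomly varying size, stratified by hospital and AKI grade (1 versus 2), with block sizes withheld from investigators. Six strata are workable with 162 patients.
2. In section 2.10, add hospital and AKI grade as factors in the primary Scr model. In a repeated-measures ANOVA each needs its interaction with visit, because the treatment effect on change lies in the arm-by-visit term. Both factors are known at baseline, so no new data are needed.
3. If the existing list is a shuffled 54/54/54 sequence, say so.
4. If enrolment is under way, use the new list for the remaining patients. If it is complete, make the model adjustment alone, before the data are analysed by arm.

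The cost is a new list from the independent biostatistician and an amendment. Allocation becomes slightly more predictable, which varying concealed block sizes limit and central allocation would limit further. The model adjustment costs almost nothing.

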### 2.5. Interventions

Patients diagnosed with CKD stages 2–4 complicated with AKI grades 1–2 will be enrolled after signing written informed consents. They will be randomly divided into the RG group, the CHF group, and the RG + CHF group. To minimize potential loss and help participants conduct the trial smoothly, three group patients will receive study behavior and health education, and they will also be told possible risks and benefits, their rights and obligations, and how to handle an emergency situation. All patients will receive a low-salt, high-quality, and low-protein diet (protein intake 0.6–0.8 g/kg/d). Also, they will receive general treatments, whose purposes are to correct water, electrolyte, and acid-base balance disorders, control blood pressure, improve anemia, and correct renal bone diseases. Designed investigations will keep in touch with participants regularly and assist them to receive treatment and testing on schedule.

The RG group will be given RG 1.8 g added to 0.9% normal saline or 5% glucose 250 ml for injection, intravenous injection (IV), once per day for 2 weeks. The CHF group will be given CHF orally, twice per day for 2 weeks. At the same time, the concentrated solution of CHF will be given an enema, once per day for 5 days, and then rest for 2 days, 5 times in a week. The RG + CHF group will be the combination of the RG group and the CHF group, and intervention methods are the same as the above.

Pharmaceutical compositions of CHF are mainly as follows: prepared rhubarb (Zhida Huang), Ligusticum wallichii (Chuan Xiong), Codonopsis pilosula (Dangshen), Coptidis rhizome (Huanglian), Smilacis glabrae (Tufuling), etc. RG will be produced by Chongqing Yaoyou Pharmaceutical Co. Ltd., and CHF will be produced by Jiangyin Tianjiang Pharmaceutical Co. Ltd. Therefore, the quantity and quality of medicine can be effectively guaranteed.

Related examinations will be conducted and collected at baseline, every 1 week during treatment. Patient information will be recorded, and efficacy-related examinations, mechanism-related indicators, safety-related indicators, and drug management will be closely observed. Measured items and time points are listed in Table 3.

### 2.6. Outcome Measures

The primary evaluation outcome will be the change in the slope of Scr over 2 weeks. Posttreatment changes in BUN, eGFR, and urinary AKI biomarkers including urinary NGAL, IL-18, *γ*-GT, and TCM symptoms will be the secondary evaluation outcomes.

In addition to the secondary evaluation outcome, inflammatory indicators including TNF-*α* and IL-6 and oxidative stress indicators including heme oxygenase-1 (HO-1), malondialdehyde (MDA), and superoxide dismutase (SOD) will also be measured before and after treatment.

Safety outcomes and vital sign indicators (electrocardiogram, blood routine, urine routine, serum potassium, hemoglobin, etc.) will be recorded once before and 2 weeks after medication. Meanwhile, AEs will be closely observed, meticulously recorded, and properly handled by investigators throughout the study.

HCG: human chorionic gonadotropin; Scr: serum creatinine; BUN: blood urea nitrogen; eGFR: estimated glomerular filtration rate; TCM: traditional Chinese medicine; NGAL: neutrophil gelatinase-associated lipocalin: IL-18: interleukin-18; *γ*-GT: gamma-glutamyl transpeptidase; IL-6: interleukin-6; TNF-*α*: tumor necrosis factor-*α*; HO-1: heme oxygenase-1; MDA: malondialdehyde; SOD: superoxide dismutase.

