**Methods:**

This is a multicenter randomized controlled clinical trial. We intend to enroll 162 participants, and these participants will be divided into the RG group, the CHF group, and the RG + CHF group randomly assigning 1 : 1 : 1 principle. The RG group will be general treatments combining RG, the CHF group will be general treatments combining CHF, and the RG + CHF group will be general treatments combining RG and CHF. The duration of treatment will last two weeks. The primary evaluation outcome will be the change in the slope of serum creatinine (Scr) over 2 weeks. Secondary evaluation outcomes include changes in blood urea nitrogen (BUN), estimated glomerular filtration rate (eGFR), urinary AKI biomarkers (neutrophil gelatinase-associated lipocalin (NGAL), interleukin-18 (IL-18), gamma-glutamyl transpeptidase (*γ*-GT), etc.), traditional Chinese medicine (TCM) symptoms, inflammatory indicators, and oxidative stress indicators. Meanwhile, the vital sign indicators and adverse events (AEs) will be closely observed. These dates will be meticulously recorded and properly handled by investigators throughout the study. *Discussion*. This study will provide convictive research-derived data to evaluate clinical efficacy and safety of CHF combing RG for CKD stages 2–4 complicated with AKI grades 1–2 and provide an evidence-based recommendation for clinicians. The timely completion of this trial will provide a novel drug treatment method for A on C. This trial is registered with ChiCTR2100043311 and registered on February 9, 2021.

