### 2.10. Statistical Analysis

The principal analysis will be conducted on a full analysis set (FAS), which consists of participants randomly allocated into two groups. Participants completing and complying well with the study protocol without major violation will be referred to the per-protocol population. All participants taking test drugs will be enrolled in safety analysis and conform with the ITT principle.

For non-normally distributed variables, mean ± standard deviation or median will be brought to describe continuous variables. Categorical variables will be presented in the form of numbers and percentages. The difference in Scr will be tested using the one-way ANOVA with repeated measures. The secondary outcomes will be compared between two groups using the independent-samples Student's *t*-tests for normally distributed continuous data and using Pearson's chi-square test (or Fisher's exact test if cell count <5 in any cell) for categorical data. Two-sided tests will be used for all statistical tests, and *P* < 0.05 will be considered statistically significant. SPSS (version 21.0) software will be used to carry out statistical analysis by a biostatistician not involved in the study. No additional analyses or interim analysis will be performed.

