**RG group**			
**CHF group**			
**RG** **+** **CHF group**			
Effectiveness observation			
**Renal functions (Scr, BUN, eGFR)**	×		×
**AKI biomarkers (NGAL, IL-18, *γ*-GT)**	×		×
**TCM symptoms**	×		×
Mechanism observation			
**Inflammatory indicators (IL-6, TNF-*α*)**	×		×
**Oxidative stress indicators (HO-1, MDA, SOD)**	×		×
Safety observation			
**Electrocardiogram**	×		×
**Blood routine**	×		×
**Urine routine**	×		×
**Fecal routine and occult blood test**	×		×
**Serum potassium**	×		×
**Hemoglobin**	×		×
**Adverse events**		×	×
Drug management			
**Drug distribution**	×	×	×
**Drug recycling**		×	×
**Drug count**		×	×
Research conclusion			×

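### The primary outcome is described in different ways, and a change in slope does not fit the two scheduled Scr measurements

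*Protocol article*

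**What the plan says.** The primary variable appears in four places in the protocol article.

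- **Abstract, Methods:** "The primary evaluation outcome will be the change in the slope of serum creatinine (Scr) over 2 weeks".
- **Section 2.6, Outcome Measures:** "The primary evaluation outcome will be the change in the slope of Scr over 2 weeks".
- **Section 2.9, Sample Size Estimation:** "The sample size will be calculated according to the primary outcome of baseline Scr change". The inputs that follow are a mean Scr of 160.39 μmol/l, an SD of 44.43 μmol/l, and an Scr in the combination arm more than 30 μmol/l below each of the other two arms.
- **Section 2.10, Statistical Analysis:** "The difference in Scr will be tested using the one-way ANOVA with repeated measures".

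On timing, section 2.5 says: "Related examinations will be conducted and collected at baseline, every 1 week during treatment". The same paragraph closes with "Measured items and time points are listed in Table 3". In Table 3, under effectiveness observation, the row "Renal functions (Scr, BUN, eGFR") is marked at baseline and at 2 weeks, and its week-1 cell is empty. The week-1 column is in use elsewhere: combined medication, adverse events, and drug distribution, recycling and count are all marked there.

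**The concern.** A change in slope compares two slopes within a patient, for example before and during treatment, or early and late in treatment. That takes at least three Scr values or a slope from before treatment. Table 3 provides two values, and the article defines no pre-treatment slope.

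The other sections do not settle what was meant. One names a change and uses the mean and SD of a level, and the other names only a difference. With two visits, a repeated-measures ANOVA can test the change (the group-by-time term) or the average level (the group term), so naming the test does not identify the variable.

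At stake is whether the primary variable is fixed before the data are seen. Section 2.4 says that treatment cannot be blinded because no placebo is used. Masked laboratory staff and an objective assay protect the measurement, but not the choice of which function of it is primary.

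**Working it through.** **1. What the schedule yields.** With Scr at weeks 0 and 2, the least-squares slope has weights (−0.5, +0.5), so

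slope = (Scr at week 2 − Scr at week 0) / 2.

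This is the change from baseline on another scale. No second slope is available to subtract from it.

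**2. The plan's own figure.** Inputs from section 2.9: difference 30, SD 44.43, α 0.05, power 0.90, dropout 20%, three arms. Take arm means 0, 0 and −30. Their mean is −10 and the squared deviations are 100, 100 and 400, with average 200.

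- f² = 200 / 44.43² = 0.1013
- noncentrality = 3n × f² = 13.07 at n = 43
- F-test power on 2 and 3n − 3 degrees of freedom: 0.9025 at n = 43 and 0.895 at n = 42
- 43 / 0.8 = 53.75, rounded up to 54

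The stated 54 per arm is reproduced as a three-group ANOVA on a variable with SD 44.43, the SD given for Scr level. No SD of a change or slope enters.

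**3. Slope against change.** Halving the change halves both the difference (30 to 15) and the SD, so the test statistic does not move. At a correlation of 0.3, for instance, power is 0.744 on either scale.

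**4. Change against week-2 level.** The article gives no SD for a change and no correlation between visits. Assume an SD of 44.43 at both visits and a correlation ρ between baseline and week 2. Then

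- SD of change = 44.43 × √(2(1 − ρ))
- residual SD after baseline adjustment ≈ 44.43 × √(1 − ρ²)

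Power with 43 evaluable per arm and a difference of 30:

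| Primary variable | Test | ρ = 0.3 | ρ = 0.5 | ρ = 0.7 |
|---|---|---|---|---|
| Change: SD | – | 52.57 | 44.43 | 34.42 |
| Change | pairwise t, two-sided 0.05 | 74% | 87% | 98% |
| Change | three-group F | 78% | 90% | 99% |
| Week-2 level (SD 44.43) | pairwise t, two-sided 0.05 | 87% | 87% | 87% |
| Week-2 level (SD 44.43) | three-group F | 90% | 90% | 90% |
| Week-2 adjusted for baseline: residual SD | – | 42.38 | 38.48 | 31.73 |
| Week-2 adjusted for baseline | pairwise t, two-sided 0.05 | 90% | 95% | 99% |

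Since √(2(1 − ρ)) = 1 at ρ = 0.5, change and level have equal power there. Below 0.5 the change score falls short of the planned 90%, and above it the change score exceeds it. Since 1 − ρ² = (1 − ρ)(1 + ρ) is never larger than 2(1 − ρ), the adjusted analysis is never less precise than the change score.

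**5. Would a week-1 Scr alter this?** A least-squares slope over weeks 0, 1 and 2 has weights (−0.5, 0, +0.5). The week-1 value drops out and the slope is again the change divided by 2.

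**The case against.** The strongest reply is that the article uses the word slope loosely for the rate of change over two weeks. Read so, the outcome can be computed from the two planned values, sections 2.6 and 2.9 name the same quantity, and a group-by-time comparison in section 2.10 would test it. This stands in part. A reader might infer that the primary outcome cannot be computed at all, but that is true only of a literal slope-minus-slope. The wording is at fault and the data remain usable. The reply does not remove the level-based inputs of section 2.9, and it needs a reading that the text does not state.

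Other stronger readings are tempting and also lack support.

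- **That choosing between slope and change could alter the p-value.** From two points they differ by a constant factor, so it could not. Only change against level can differ.
- **That section 2.5 flatly contradicts Table 3 by promising a weekly Scr.** It names no test and refers to Table 3 for items and time points, and Table 3 has other week-1 entries. It is ambiguous and needs clarifying.
- **That the registered endpoint is faulty.** The article gives a registration number but not the registry's outcome wording, so nothing can be said about it.
- **That a week-1 Scr with a random-slope model would rescue the slope.** In complete balanced data it gives the same estimate of the group slopes, and Table 3 has no laboratory test at week 1, so it would add a blood sample.
- **That the sample size is miscalculated on this account.** The figure of 54 is reproduced.

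It could also be said that an article may leave such detail to a full protocol or analysis plan. That does not answer the point, because the statements in this document disagree about the primary variable. An analysis plan would have to override at least one of them.

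**Conclusion.** The point holds as an inconsistency in the primary outcome. Taken literally, the outcome in the abstract and section 2.6 does not fit Table 3. Taken loosely, it is the change from baseline, while the sample size rests on an Scr level.

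The practical consequence is the difference between change and week-2 level. Over assumed correlations of 0.3 to 0.7, change-score power runs from 74% to 98% in a pairwise comparison, against 87% for the level. With the three-group F-test it runs from 78% to 99%, against 90%. At a correlation of 0.5 there is no difference in power. These figures assume equal SDs of 44.43 at both visits and 43 evaluable patients per arm, and the correlations are not document figures.

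Because the conflict concerns the primary variable in a trial whose treatment is not blinded, it should be settled before any outcome data are seen.

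**What to change.** Delete the reference to a change in slope and use one definition in the abstract and sections 2.6, 2.9 and 2.10. The preferred wording is: Scr at week 2, compared between the arms with adjustment for baseline Scr. A plainly defined change from baseline to week 2 would also remove the inconsistency and lies closer to the wording of section 2.9, but its power is no higher than that of the adjusted analysis and is clearly lower at low correlations. Section 2.9 should state that its SD belongs to the chosen variable or, for a change score, the correlation assumed.

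Clarify the sentence on weekly examinations in section 2.5 against Table 3, so that sites know whether Scr is measured at week 1.

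The cost is a change of wording in the protocol. The preferred definition uses the two Scr measurements already planned and needs no extra visit, blood sample or patients.
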